# Effect of electro-acupuncture on lateralization of the human swallowing motor cortex excitability in healthy subjects: study protocol for a single-blind, randomized controlled trial

**DOI:** 10.1186/s13063-019-3267-x

**Published:** 2019-03-21

**Keywords:** Electro-acupuncture, Lateralization of the swallowing motor cortex, Dysphagia, Stroke, Transcranial magnetic stimulation

## Abstract

**Background:**

Numerous randomized controlled trials on the effects of electro-acupuncture have been conducted to treat dysphagia as a sequela of stroke. However, the normal physiological mechanisms of swallowing and the pathological mechanisms of dysphagia are not fully understood. The purpose of this study is to investigate whether lateralization of the human swallowing motor cortex excitability in healthy subjects will be influenced by electro-acupuncture to Lianquan (CV 23) and Fengfu (GV 16), which may provide insight into the pathological mechanisms of dysphagia after stroke.

**Methods:**

We designed a single-blind, randomized, sham-controlled trial in which 40 healthy subjects will be recruited. Subjects will be randomized 1:1 into two groups: the electro-acupuncture group and the sham-control electro-acupuncture group. The swallowing motor cortex will be located in both groups using a neuroimaging navigation system. Then left and right cortical stimulation will be measured by transcranial magnetic stimulation (TMS) before and after electro-acupuncture or sham electro-acupuncture. The electro-acupuncture or sham electro-acupuncture interventions will last for 15 min. The primary outcome measure will be percent change in the resting motor threshold (RMT) of the mylohyoid. The secondary outcome measures will be the amplitude (μV) and latency (ms) of the motor evoked potential (MEP) of the mylohyoid as a proxy for the TMS evoked potential. All outcomes will be measured at baseline and after the electro-acupuncture or sham electro-acupuncture treatment.

**Discussion:**

The aim of this trial is to explore whether lateralization of the human swallowing motor cortex excitability in healthy subjects is present, and to determine if electro-acupuncture to acupuncture points Lianquan (CV 23) and Fengfu (GV 16) will exert an effect on it under normal physiological conditions.

**Trial registration:**

Chinese Clinical Trial Registry, ChiCTR-IOR-17011359. Registered on 11 May 2017.

**Electronic supplementary material:**

The online version of this article (10.1186/s13063-019-3267-x) contains supplementary material, which is available to authorized users.

## Background

The main role of swallowing is to transport food and drink from the oropharynx to the stomach while preventing aspiration [1]. Healthy adults swallow approximately 800 to 2400 times per day. Swallowing is a complex process comprised of five distinct phases [2]. Research in humans has demonstrated that automatic and volitional swallowing are under the control of the human cerebral cortex and are associated with activation of several spatially and functionally distinct cortical regions [3]. Oropharyngeal dysphagia (OD) is a common sequela of stroke that occurs if any phase in the swallowing process is disrupted. To fully understand the sensory motor functions of swallowing in the pathological state (as a sequela of stroke in patients with OD), lateralization of the human swallowing motor cortex must be examined in the normal physiological state in healthy subjects. Overall, 27% of the elderly population has OD which affects 47.5% of the hospitalized elderly (of those up to 91% have community-acquired pneumonia) and 51% of nursing home residents [4–9]. Dysphagia as a sequela of stroke potentiates serious health conditions such as aspiration, aspiration pneumonia, and malnutrition, which may lead to depression, anxiety, decreased quality of life, and death [10].

Lateralization of the functions and structures of the human and animal brain has been known since the 1860s when the French surgeon Paul Broca discovered that the two cerebral hemispheres have different functions [11]. This important finding established the foundation for research examining pathological processes in the brain regions involved in stroke, particularly the cerebral hemispheres [12, 13]. Scientists then began to examine cerebral hemispheric lateralization in healthy subjects under normal physiological conditions to uncover the mechanisms involved in this process. In the last 20 years, researchers worldwide have examined the swallowing motor cortex and its role in diseases that present with dysphagia using transcranial magnetic stimulation (TMS) in healthy subjects as well as in subjects with dysphagia as a sequela of cerebral hemisphere stroke. Whether patients suffer from dysphagia after a cerebral hemisphere stroke depends on the swallowing motor cortex map size in the undamaged cerebral hemisphere. Also, recovery from dysphagia is associated with the reorganization of the swallowing motor cortex in the undamaged cerebral hemisphere [14–17]. Increasing sensory input to the motor cortex via electrical stimulation results in an increased ability to swallow and hastens rehabilitation after stroke. The purpose of this study is to investigate whether lateralization of the human swallowing motor cortex excitability in healthy subjects under normal physiological conditions will be influenced by electro-acupuncture. Results may provide insight into the pathological mechanisms of dysphagia after stroke.

A 2017 systematic review of 71 studies, with over 6000 subjects enrolled, examined the efficacy of acupuncture for the treatment of OD as a sequela of stroke. Findings indicated that: 1) in a pooled analysis, acupuncture had a statistically significant effect compared with the controls, with moderate heterogeneity (*p* < 0.0001); and 2) the efficacy rate of acupuncture was three times that of the controls, demonstrating that acupuncture was efficacious for the treatment of dysphagia after stroke [18].

Electro-acupuncture has been used to treat dysphagia as a sequela of stroke to enhance swallowing ability [19]. One study used a microcurrent device that emitted a weak electrical signal of less than 1 μA attached with electrodes to acupuncture needles. Findings showed that electro-acupuncture produced a more widespread signal and therefore may be more effective than manual acupuncture [20].

After examination with TMS, acupuncture to Hegu (LI 4) demonstrated a statistically significant reduction in right hemisphere motor cortex excitability (*p* = 0.048) and an increase in left hemisphere motor cortex excitability which was not statistically significant (*p* = 0.16) [21]. Also, acupuncture to right Yanglingquan (GB 34) decreased the excitability of the left hemisphere motor cortex (*p* = 0.047) [22]. Both these studies demonstrated that acupuncture administered to acupuncture points on the extremities can modulate the lateralization of motor cortex excitability and provide the necessary foundation to study lateralization of the swallowing motor cortex excitability with electro-acupuncture.

Lianquan (CV 23) is an acupuncture point on the anterior of the surface of the neck directly superior to the laryngeal prominence, in the depression at the upper margin of the hyoid bone. It is at the base of the tongue and level with the pharynx. CV 23 is also located where the mylohyoid (which is a paired muscle running from the hyoid bone to the mandible and which forms the floor of the mouth) inserts into the hyoid. The mylohyoid is responsible for swallowing and speaking.

Fengfu (GV 16) is 1 cun directly above the midpoint of the posterior hairline in the depression below the external occipital protuberance. GV 16 is just ventral and rostral to the medulla oblongata (the center of deglutition) which controls swallowing [23].

Plasticity of the swallowing motor cortex is imperative for the recovery of patients with OD after stroke. It requires stimulation from sensory input and an undamaged map area. Studies examining the mechanisms of electro-acupuncture on OD as a sequela of stroke are difficult to perform. Therefore, lateralization of the human swallowing motor cortex excitability with electro-acupuncture in healthy subjects must be performed. The aim of this trial is to explore whether lateralization of the human swallowing motor cortex excitability in healthy subjects is present. We will then investigate the effects of electro-acupuncture on lateralization of the human swallowing motor cortex excitability by recording the resting motor threshold (RMT) and the motor evoked potential (MEP) changes in an electro-acupuncture and a sham electro-acupuncture group. We hypothesize that after administering electro-acupuncture to healthy subjects there will be a decrease in the RMT and an increase in the amplitude of the MEP in the swallowing motor cortex. This will demonstrate the activation of the swallowing motor cortex by electro-acupuncture. Results of this study will both help identify the swallowing mechanism in healthy subjects and enhance the understanding of the pathological mechanisms of OD as a sequela of stroke. It is possible the other undamaged hemisphere map area may be activated by electro-acupuncture as well, which may ultimately demonstrate mechanisms of cerebral functional reorganization and cerebral plasticity in OD as a sequela of stroke.

## Methods/design

### Study design

This will be a single-blind, randomized controlled trial (RCT). Electro-acupuncture will be compared with sham electro-acupuncture to determine if electro-acupuncture has an effect on lateralization of the human swallowing motor cortex excitability. Forty healthy subjects will be blinded to the study condition. This RCT will be conducted at the South China Research Center for Acupuncture and Moxibustion from April 2017 to April 2019. This trial has been registered with the Chinese Clinical Trial Registry (ChiCTR-IOR-17011359). The study design is presented in the flowchart in Fig. 1. The Standard Protocol Items: Recommendations for Interventional Trials (SPIRIT) checklist is provided as Additional file 1.

**Fig. 1 Fig1:**
[figure not shown]
Consort flow chart. MEP motor evoked potential, RMT resting motor threshold, TMS transcranial magnetic stimulation

### Recruitment

The participants will be recruited by posting study recruitment flyers in classrooms at Guangzhou University of Chinese Medicine. Participants will contact the recruitment staff by telephone or email. Recruitment staff will be responsible for the enrollment of participants. If they meet the study criteria, they will be invited to the South China Research Center for Acupuncture and Moxibustion to undergo the study.

### Inclusion criteria

Participants who meet the following inclusion criteria will be eligible to participate in this study: 1) male or female; 2) between 18 and 25 years of age; 3) have no history of health problems, swallowing disorders, or pain with swallowing; 4) have a negative Kubota Water Swallow Test (test for OD); 5) have a normal Mini-Mental State Examination (MMSE) (a measure of cognitive impairment); 6) have a body mass index (BMI) between 18.5 and 24 kg/m^2^; and 7) be willing to sign the informed consent form.

### Exclusion criteria

Subjects will be excluded if they have any of the following conditions: 1) a history of major diseases, surgeries, or severe traumas; 2) swallowing disorders of any etiology; 3) presence of laryngeal organic diseases such as severe pharyngitis, rhinitis, or upper respiratory infection, nasal polyps, or deviated nasal septum; 4) difficulty breathing; 5) presence of viral hepatitis, HIV, or other blood infections; 6) presence of a cardiac pacemaker or other implanted devices such as brain metal electrodes (except titanium), cochlear implants, or pulse generators; 7) conditions that may potentiate seizures such as a history of epilepsy, sleep deprivation, alcohol dependence, or ingestion of olanzapine or lithium carbonate; and 8) pregnancy or lactation.

### Randomization and allocation concealment

Forty healthy subjects will receive TMS bilaterally on both swallowing motor cortices. Then they will be randomized 1:1 to an electro-acupuncture group or sham electro-acupuncture group. Randomization will occur according to a computer randomization program generated by the Package for Encyclopedia of Medical Statistics (PEMS) 3.1 software (West China School of Public Health, Sichuan, China) and overseen by an independent statistician. Subjects will be sequentially assigned a random number from 1 to 40. Opaque sealed envelopes will be used for the randomization and allocation. The envelopes will be numbered consecutively with a serial number on the outside and will contain the allocation information. An envelope will be opened when a subject enters the study after informed consent is obtained. Participants will be allocated to one of the two groups and receive an intervention according to their group allocation. The random allocation sequence and the opaque sealed envelopes will be kept by two different researchers.

### Blinding

Due to the specific nature of acupuncture, it is difficult for acupuncture researchers to be blind to the study condition. Consequently, in order to maintain blinding the subjects, researchers and the statistician will be blind to the study condition, but not the acupuncturist. The data will be analyzed by two statisticians who will otherwise not be involved in this trial and are naive to all study processes.

### Study procedures

Subjects consented to the study will complete the MMSE, Kubota Water Swallowing Test, and be weighed so that BMI may be calculated in an examination room at the South China Research Center for Acupuncture and Moxibustion, Medical College of Acu-Moxi and Rehabilitation, Guangzhou University of Chinese Medicine. They will sit on the treatment couch facing the neuroimaging navigation system and TMS machine to enable location of the correct brain regions. Subjects will be instructed not to swallow, cough, or speak when receiving TMS as these actions will cause artifacts and render the results invalid.

Surface electrodes will be placed on the skin over the mylohyoid after being sanitized with skin scrub. Mylohyoid electromyography (EMG) responses will be detected using two pairs of bipolar silver-silver chloride electrode (10 mm diameter, 1.5 m cable 12/package, DIN Style, Nicolet, USA); the surface record electrodes will be placed bilaterally on each side of the mylohyoid, and the reference electrodes will be placed directly next to them (1 cm). Two pairs of ground wire disc electrodes (1. 25 m cable, 1/package, DIN Style) will be placed 2 cm from both corners of the mouth to reduce interference to the EMG signal. All electrodes will be checked every 15 min to ensure that they are in contact with the skin and underlying muscles.

### Navigation

The subject’s magnetic resonance image (MRI) (3.0 T) T1 file will be scanned at Guangdong Provincial Hospital of Chinese Medicine with an MRI scanner (signa EXCITE 3.0 T HD, IGE, USA). This MRI T1 file will be imported into the neuroimaging navigation system (Brainsight^*®*^ 2.3.3.dmg). Brainsight^®^ will then be applied to reconstruct a three-dimensional (3D) brain. The reconstruction is shown in Fig. 2. The Polaris System will be used to collect cortical topographical landmarks of the head, which allows the external near infrared system to follow in real time the stimulator coil of the TMS. An image of a swallowing motor cortex navigation is shown in Fig. 3.

**Fig. 2 Fig2:**
[figure not shown]
Three-dimensional brain reconstruction

**Fig. 3 Fig3:**
[figure not shown]
Neuroimaging navigation of the swallowing motor cortex

### Transcranial magnetic stimulation

Transcranial cortical stimulation will be performed at each session using a commercially available magnetic stimulator that is connected to a figure-of-eight coil before and after the intervention. TMS allows focal stimulation to areas of the cerebral cortex up to a maximum of 2.2 T.

### Intervention

Electro-acupuncture or sham electro-acupuncture will be performed for one 15-min session by an experienced doctor of acupuncture. A sterile acupuncture needle (length 25 mm, diameter 0.30 mm; Huatuo, Suzhou Medical Supply Factory Co. Ltd., Suzhou, China) will be inserted into CV 23 to a depth of 0.5 to 0.8 cun, and into GV 16 to a depth of 0.5 to 1 cun. The researcher will then apply electro-acupuncture by connecting an acupuncture point nerve stimulator (HANS-200A) to the needles with a frequency of 2 Hz for 15 min; the intensity of electro-acupuncture will be set according to the maximum tolerated intensity of each subject (between 0.9 mA and 3 mA) ([name]. Effect of Electroacupuncture at Acupoints on the Conception Vessel and Governor Vessel on the Swallowing Motor Cortex in Humans, unpublished). To maintain study fidelity, all researchers will receive training on the study methods, techniques, and study monitoring. All research staff will be tested after training to ensure they can consistently replicate the protocol.

### Sham electro-acupuncture

For sham electro-acupuncture, the K Streitberger placebo needle (Huatuo, Suzhou Medical Supply Factory Co. Ltd., Suzhou, China) will be applied at CV 23 and GV 16. The K Streitberger placebo was invented by Streitberger in 1998, which is a validated and reliable single-blind acupuncture needle used to investigate the effects of acupuncture [24]. This single-blind placebo needle is widely used in acupuncture research. The HANS acupuncture point nerve stimulator will be connected to the placebo. The RMT and MEP of the mylohyoid will be measured before and after electro-acupuncture or sham electro-acupuncture. Previous studies have reported using TMS to study the cortical topography of the human swallowing musculature in healthy subjects by recording RMT and MEP [14].

### Outcome measures

#### Primary outcome measure

TMS has been widely used for assessing cortical excitability. At the same time, the RMT, as a TMS measure, can be used as an indicator of cortical excitability, which is reliable in single pulse TMS measures [25, 26]. Thus, the primary outcome measure will be the percent change in the RMT of the mylohyoid at baseline and after the electro-acupuncture or sham electro-acupuncture treatment. The RMT of the mylohyoid will be delivered by a TMS pulse every 30 s bilaterally to the left and right swallowing motor cortices, respectively, for 10 pulses in the fully relaxed state. The MEP of the mylohyoid should be greater than or equal to 30 μV for at least half, or 5 of the 10 TMS pulses. The RMT is defined as the minimum intensity that is needed to elicit the MEP ≥ 30 μV in at least 50% of pulses.

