### Sample size calculation

The sample size was calculated based on a pretest from a reference in this field, where the sample size was 19.36 and calculated according to the statistical formula: $$ n=\frac{2\left[{\left(\upalpha +\upbeta \right)}^2{\sigma}^2\right]}{{\left({\upmu}_1-{\upmu}_2\right)}^2} $$ where *n* was the sample size of the treatment group/control group, α is the significance level, β is the power of the test, σ is the population variance (SD) and μ_1_ − μ_2_ is the smallest effect of interest. In this study, α = 0.05, β = 0.80 (80%), σ was estimated at 13.07, and μ_1_ − μ_2_ was the RMT of the swallowing-related muscle groups (the most important index to evaluate lateralization of the human swallowing motor cortex excitability). This was the minimum clinical significance value for the RMT of the swallowing muscles that was calculated from previous trials and expert assessments, based on the primary clinical data, which was estimated at 3.57 ([name]. Effect of Electro-acupuncture at Acupoints on the Swallowing Motor Cortex in Humans, unpublished). Therefore, a sample size of 19.36 is needed in each group (electro-acupuncture and sham acupuncture). We will include 20 subjects per group condition.

Forty healthy subjects will be randomized 1:1 to the electro-acupuncture or the sham electro-acupuncture groups. Both groups will receive TMS (Magstim 200, Magstim Co. Ltd., Whitland, Wales, UK). The RMT and the MEP of the mylohyoid will be recorded using EMG (Nicolet Viking Quest, Wisconsin, USA) before and after one 15-min electro-acupuncture or sham electro-acupuncture treatment. The whole study procedure from assessing eligibility to completion of the treatment will last between 1 and 2 h.

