### Statistical analysis

The RMT and MEP statistical analysis will be performed using the Statistical Package for Social Science (SPSS) version 17.0 (SPSS Inc., Chicago, IL, USA). Levene’s test for homogeneity of variance will be applied. If measurement data are normally distributed then the independent *t* test will be used to analyze between-group differences for each subject before and after electro-acupuncture or sham electro-acupuncture, and between the electro-acupuncture group and the sham electro-acupuncture group. Otherwise, the Wilcoxon rank sum test for a nonparametric distribution will be used. A *p* value less than or equal to 0.05 will be considered statistically significant.

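### Percent change in RMT, compared without baseline adjustment, leaves the result open to chance baseline imbalance and gives up precision when the pre-post correlation is moderate

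*Protocol article*

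**What the plan says.** **Endpoint.** Under Primary outcome measure, "the primary outcome measure will be the percent change in the RMT of the mylohyoid at baseline and after the electro-acupuncture or sham electro-acupuncture treatment". It is the same in the Abstract. RMT is the lowest intensity that gives an MEP of at least 30 μV in at least half of 10 pulses.

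**Test.** Under Statistical analysis, if the data are normal, "the independent *t* test will be used to analyze between-group differences". If not, "Otherwise, the Wilcoxon rank sum test for a nonparametric distribution will be used". Neither test uses a covariate, and no section names baseline RMT as a covariate or stratification factor.

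**Baseline.** Randomization and allocation concealment puts bilateral TMS before the 1:1 allocation, so baseline RMT exists for all 40 subjects.

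**Planning figures.** Sample size calculation gives "α = 0.05, β = 0.80 (80%), σ was estimated at 13.07" and a smallest effect of interest "which was estimated at 3.57", with 20 subjects per group. It does not say whether these figures are RMT units or percentage points. Mean RMT and the pre-post correlation are not given.

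**The concern.** Dividing by baseline looks like an adjustment for baseline, but in general it is not one. Baseline RMT is a threshold estimated from a few pulses, so it carries measurement error, and it is also the denominator. A subject whose baseline is low by chance tends to rise afterwards and scores a positive percent change; a subject with a high baseline tends to do the opposite. The score therefore remains negatively correlated with baseline.

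Two consequences follow for an unadjusted comparison with 20 per arm. Any chance difference in baseline between the arms passes partly into the observed contrast. The outcome also carries variation that a baseline covariate would remove. The protocol fixes both the endpoint and its test, so this is a stated choice and not a detail left to an analysis plan.

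**Working it through.** **Inputs.** SD 13.07, target difference 3.57 and 20 per arm come from Sample size calculation. Assumptions: both figures are in RMT units; 13.07 is the between-subject SD before and after treatment; mean RMT μ is 50 to 70; r is 0.5 to 0.95.

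**1. The protocol's own figure.** The printed formula with the literal values 0.05 and 0.80 gives 2 × 0.85² × 13.07² / 3.57² = 19.37, against 19.36 stated. With the normal quantiles that the formula needs, the same inputs give 211 per group (two-sided). That is a separate point. It matters here only because little precision is available to give away.

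**2. Size of a chance imbalance.** The standard error of the baseline difference is 13.07 × √(2/20) = 4.13, which is larger than the target of 3.57. About one trial in three will exceed one standard error in either direction.

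**3. What the imbalance does.** With no treatment effect and regression to the mean, the expected percent change at baseline b is 100(1 − r)(μ − b)/b. Near b = μ its slope is −100(1 − r)/μ. A one-standard-error imbalance shifts the contrast by 100(1 − r) × 4.13/μ percentage points, against a target of about 100 × 3.57/μ. The mean cancels, so the share is (1 − r) × 4.13/3.57:

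- r = 0.5: 58%
- r = 0.7: 35%
- r = 0.9: 12%

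To first order this equals the result for a raw change score. Simulation picks up the curvature of 1/b and gives about 55-68%, 32-38% and 9-11%. Normal data with mean 50 give shifts of 5.3, 3.3 and 1.0 points. Against 3.57/50 = 7.1 points these are 74%, 46% and 15%. The shares are higher because the normal model admits very low baselines, and because 3.57/μ is smaller than the expected percent-change contrast (the mean of 1/b exceeds 1/μ).

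**4. Remaining dependence on baseline.** With normal data and no effect, the simulated correlation of baseline with percent change is −0.52, −0.41, −0.24 and −0.17 at r = 0.5, 0.7, 0.9 and 0.95.

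**5. Validity.** In simulation without an effect, the mean contrast is about 0 and type I error is 0.047 to 0.052.

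**6. Precision.** For a raw change score, the efficiency of ANCOVA relative to change is 2(1 − r)/(1 − r²) = 2/(1 + r), which is 1.33, 1.18 and 1.05 at r = 0.5, 0.7 and 0.9. Simulation against percent change gives about 1.3-1.5, 1.1-1.3 and near 1. Power at 20 per arm (normal data, mean 50, effect 3.57, two-sided 0.05):

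| r | Percent change, t test | ANCOVA, raw RMT |
|---|---|---|
| 0.5 | 0.125 | 0.162 |
| 0.7 | 0.179 | 0.214 |
| 0.9 | 0.437 | 0.472 |
| 0.95 | 0.726 | 0.756 |

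**7. Other data models (mean 50).**

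- *Lognormal data with regression to the mean:* percent change matches or slightly beats raw ANCOVA at high r (0.505 vs 0.501 at r = 0.9; 0.803 vs 0.780 at 0.95). ANCOVA on log RMT does not lose (0.520 and 0.805).
- *Purely proportional noise without regression to the mean:* percent change is uncorrelated with baseline and slightly better than raw ANCOVA (0.504 vs 0.473 at r = 0.9) and log ANCOVA (0.496).

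**The case against.** Four arguments carry weight.

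- **Randomisation already protects the comparison.** A reader might infer that the endpoint biases the trial. It does not: chance imbalance is part of the sampling error that the t test reflects. What stands is a shift conditional on the imbalance that happens to occur.
- **The loss of precision is not universal.** Both measurements fall within one procedure of 1 to 2 hours, and the protocol calls RMT reliable, so r of 0.9 or more is plausible. There the gain is small and can reverse slightly if the scale is mismatched. This stands, and it is why the scale must be chosen in advance.
- **The size rests on figures the protocol does not give.** If 13.07 and 3.57 are percentage points, the shares above do not apply. This also stands.
- **Timing.** Trial status places completion by December 2018, before publication in March 2019, so replacing a registered primary endpoint may be more than a wording change. An adjusted analysis of the same endpoint meets this objection.

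A reader might also infer that the random denominator works against the hypothesis, because mean percent change is positive even with no true change. That artefact arises in both arms and largely cancels in the between-arm contrast. The phrase "test will be used to analyze between-group differences for each subject before and after electro-acupuncture or sham electro-acupuncture" is too unclear to show that a test of percent change against zero within an arm is planned.

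**Conclusion.** The point holds in a limited form. The randomised comparison is valid, but its primary analysis makes poor use of a baseline that is already measured. Under the assumptions in the working, the conditional shift is material at r of 0.5 to 0.7 and minor at 0.9. The efficiency gain from adjustment follows the same pattern. The direction is reliable wherever there is regression to the mean; the size cannot be settled from the document, because mean RMT, r and the units of the planning figures are missing. It would be wrong to conclude that adjustment rescues the sample size: with 20 per arm, ANCOVA comes near 80% power for 3.57 only if r is about 0.95 and 13.07 is a between-subject SD. The change is worth making because it costs almost nothing.

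**What to change.** Make the primary between-arm analysis an ANCOVA of post-treatment RMT, with baseline RMT of the same hemisphere as covariate. Fix the scale, raw or log, before the data are unblinded. Report percent change by arm as a descriptive summary.

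If the registered endpoint must stay, keep percent change as the outcome and add baseline RMT as a covariate. With lognormal data and mean 50, this recovers most of the gain: power goes from 0.138 to 0.159 at r = 0.5 and from 0.208 to 0.228 at r = 0.7, against 0.169 and 0.234 for ANCOVA on log RMT.

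The cost is one sentence of wording and one covariate in SPSS, with no new data or subjects. The downside is little gain if r is 0.9 or higher. The sample-size calculation needs its own correction.
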